## **E3 Safety**

### **3.a Data and Safety Monitoring Board**

A Data and Safety Monitoring Board (DSMB) will be appointed by the National Heart Lung and Blood Institute (NHLBI) to monitor subject safety and to review performance of the protocol. A DSMB charter that outlines the operating guidelines for the committee and the procedures for the interim evaluations of study data will be developed by the NHLBI and agreed upon at the initial meeting of the DSMB. Reports will be prepared regularly by the DCRI as requested by the DSMB chair. Depending upon the operational plan established by the DSMB, the report might include recruitment and retention rates, interim analyses, primary and secondary endpoints, and other information as requested by the committee. After each meeting, the DSMB will make recommendations to the NHLBI and the trial leadership about the continuation of the study.

### **3.b Study Coordinating Center or Food and Drug Administration Notification by Investigator**

No reporting (other than through the InFORM system) is required.

### **3.c Definitions of Safety Events and Reporting**

Because the only intervention in the trial is the randomized assignment of the initial test to be performed in a symptomatic subject with clinically indicated testing, the only safety events arising from the study are related to the initial test. Mild safety events are considered related to testing only up to 24 hours after the initial randomized test and will be collected and reported by site personnel. The site investigator/designee will document the safety events listed below occurring within 24 hours of initial testing and report them in the InFORM system.

In contrast, those severe events/complications related to cardiovascular testing or cardiovascular procedures that are also trial endpoints (e.g. peri-procedural MI, major bleeding, renal failure, and anaphylaxis requiring circulatory or respiratory support) will be collected throughout the duration of the trial and will be considered to be related to testing or a procedure if occurring within 72 hours.

#### **For CTA:**

1. Mild contrast reaction such as rash and hives (severe reactions including anaphylaxis or death are part of the primary endpoint)
2. Extravasation of contrast into the surrounding tissue of the extremity where the intravenous line was placed and contrast administered
3. Hemodynamic instability, including symptomatic bradycardia or hypotension, due to the beta blockade or nitrates given for the CTA scan acquisition
4. Acute bronchospasm due to the beta blockade given for the CTA scan

#### **For exercise testing during exercise ECG, stress echo, or stress nuclear:**

1. Exercise-induced hypotension with systolic BP fall greater than 20 mm Hg
2. Stress-induced symptoms that do not resolve within 20 minutes
3. Rapid atrial fibrillation that does not slow or convert with treatment

- 
4. Ventricular tachycardia
  5. Hemodynamic instability, defined as systolic BP less than 80 mm Hg
  6. Hospital admission not otherwise captured by the primary endpoint, including that precipitated by any symptomatic event (chest pain, dyspnea, etc.), persistent or worsening ischemic ECG changes, any bradycardic or tachycardic arrhythmia, or any hemodynamic changes (hypertension or hypotension)

**For stress nuclear:**

1. The above events for exercise testing
2. Any events potentially related to the use of vasodilators such as dipyridamole or adenosine, including an anaphylactic reaction to contrast agent not requiring circulatory or respiratory support

**For stress echo:**

1. The above events for exercise testing
2. Stress-induced wall motion abnormality that does not resolve within 20 minutes (despite treatment)
3. Any anaphylactic reaction to contrast agent not requiring circulatory or respiratory support

## **E4 Study Outcome Measurements and Ascertainment**

### **All-cause Mortality**

All-cause mortality is used rather than cardiac mortality to eliminate the need for possibly difficult adjudication of causes of death, especially given the relatively low mortality expected.

### **Myocardial Infarction**

Defined as either 1) an abnormal cardiac biomarker level (either troponin or CK-MB) greater than institutional upper limit of normal (ULN), and either ischemic discomfort lasting greater than 10 minutes or ECG changes indicative of ischemia or infarction, or 2) new abnormal Q waves consistent with infarction. Additionally *peri-procedural infarctions* are defined as greater than 3x ULN for serum CK-MB for PCI and greater than 5x ULN for CABG.

- an abnormal cardiac biomarker level > institutional ULN (either troponin or CK-MB), and either ischemic discomfort lasting > 10 minutes or ECG changes indicative of ischemia or infarction,

**OR**

- new abnormal Q waves consistent with infarction.

Additionally *peri-procedural infarctions* are defined as >3x upper limit of normal for serum CK-MB for PCI and >5x upper limit of normal for CABG.

---

***Unstable Angina Hospitalization***

Defined as 1) ischemic discomfort or equivalent symptoms requiring hospitalization within 48 hours of symptoms, 2) lasting greater than or equal to 10 minutes at rest, or in an accelerating pattern, 3) accompanied by dynamic ST depression, ischemia on stress testing, or significant epicardial coronary artery stenosis, and 4) considered to be myocardial ischemia upon final diagnosis.

Is defined as an event in which the final diagnosis is unstable angina or acute coronary syndrome due to myocardial ischemia and has the following criteria:

- ischemic discomfort or equivalent symptoms requiring hospitalization within 48 hours of symptoms, lasting  $\geq 10$  minutes at rest

**OR**

- ischemic discomfort or equivalent symptoms occurring in an accelerated pattern within 48 hours of hospitalization

**AND ANY OF THE FOLLOWING**

- accompanied by dynamic ST depression
- ischemia on stress testing
- significant epicardial coronary artery stenosis

***Major Complications From Cardiovascular Procedures and Diagnostic Testing That Occur Within 72 Hours***

Defined as:

- Stroke is defined as an acute focal neurological deficit of sudden onset, not reversible within 24 hours, or that resolves in less than 24 hours with clear evidence of a new stroke on cerebral imaging.
- Bleeding is defined as major based on 1 or more of the following:
  - Transfusion of greater than or equal to 2 units heterologous packed red blood cells or whole blood
  - Decrease in hemoglobin level by greater than or equal to 2.0 g/L
  - Need for reoperation or invasive intervention (e.g. evacuation of wound hematoma)
  - Bleeding at a critical anatomic site (intracranial, intraspinal, intraocular, retroperitoneal, intraarticular, pericardial, or intramuscular with compartment syndrome)
- Renal Failure is defined as new requirement for renal replacement therapy.

- 
- Anaphylaxis is defined as a severe contrast reaction requiring emergency respiratory and/or circulatory support.

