## TABLE OF ABBREVIATIONS

|         |                                                               |
|---------|---------------------------------------------------------------|
| ABI     | ankle brachial index                                          |
| ACC     | American College of Cardiology                                |
| ACRIN   | American College of Radiology Imaging Network                 |
| ACS     | acute coronary syndrome                                       |
| AHA     | American Heart Association                                    |
| BMI     | body mass index                                               |
| BP      | blood pressure                                                |
| CABG    | coronary artery bypass graft                                  |
| CAD     | coronary artery disease                                       |
| CCC     | Clinical Coordinating Center                                  |
| CD      | compact disc                                                  |
| CI      | confidence interval                                           |
| CK-MB   | creatinine kinase-myocardial band                             |
| COCATS  | Core Cardiology Training Symposium                            |
| CTA     | coronary tomographic angiography                              |
| DASI    | Duke Activity Status Index                                    |
| DCRI    | Duke Clinical Research Institute                              |
| DOFG    | Duke Clinical Research Institute Outcomes and Follow-up Group |
| DSMB    | Data and Safety Monitoring Board                              |
| DTCC    | Diagnostic Testing Coordinating Center                        |
| ECG     | electrocardiogram                                             |
| ECHO    | echocardiogram                                                |
| eCRF    | electronic case report form                                   |
| EQOL CC | Economics and Quality of Life Coordinating Center             |
| g/L     | grams per liter                                               |
| HDL     | high-density lipoprotein                                      |
| IEC     | institutional ethics committee                                |
| IRB     | institutional review board                                    |
| IVRS    | interactive voice response system                             |
| LDL     | low-density lipoprotein                                       |

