***E5 Independent Clinical Event Adjudication Committee***

An independent clinical event adjudication committee will review and adjudicate all primary endpoint events and the catheterization secondary endpoints in a blinded fashion based on the definitions presented above. If the invasive cardiac catheterization report is inconclusive, the CEC will review the catheterization films for a visual assessment of CAD. The other clinical secondary endpoint events and cumulative radiation exposure will not be adjudicated.

Primary outcome events will be documented through 60 (+/- 14) days after randomization by the site Investigator or authorized designees. After that, the DOFG or its designees will be responsible for documenting study events from 6 months until the end of the study.

---

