## 7. Endpoint Analyses

### 7.1 Primary Endpoint

The Primary Endpoint: Time from randomization to the first event in a composite of major cardiovascular events consisting of:

- Death (all-cause)
- Myocardial infarction
- Major complications from cardiovascular procedures and testing (stroke, major bleeding, anaphylaxis, and renal failure requiring dialysis)
- Unstable angina hospitalization

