#### Response Variable Definition:

Time from randomization to the first event among the components of the primary composite endpoint is measured (in days) for those who experienced an event and is calculated as the date of the first event minus the date of randomization. For

patients who do not experience any of the component events or who withdraw consent or drop out of the study before it is complete, time from randomization to the date of last contact will be used in the analysis, and those patients will be considered as censored observations in the time-to-event analysis. All possible events are carefully reviewed and adjudicated by a clinical events committee (CEC) blinded to the randomized testing assignment. Definitions for each of the events are outlined in the study protocol as well as in the CEC charter. To qualify as an endpoint, the major complications from cardiovascular testing and procedures must occur during or within 72 hours following the test or procedure.

Statistical Methods: The Cox proportional hazards model (PROC PHREG in SAS) will be the primary analytic tool for assessing outcome differences between the two randomized arms with respect to the primary composite endpoint. To appropriately account for heterogeneity among the subjects, the primary analysis for comparing the diagnostic testing arms will involve covariate adjustment using the pre-specified baseline prognostic variables listed in Appendix A. A hazard ratio and 95% confidence interval (CI) summarizing the difference in outcome between the two randomized arms will be computed using the Cox model. The level of significance for the assessment of the primary endpoint will be  $\alpha=0.05$ .

In addition to the statistical hypothesis testing, cumulative event rates will be calculated according to the method of Kaplan and Meier for each randomized arm as a function of follow-up time (time from randomization), and the estimated event probabilities will be displayed graphically.

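### Major bleeding, a primary-endpoint component, can be met by a bleed with a hemoglobin fall of only 2.0 g/L (0.2 g/dL), which looks like a unit slip

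*Supplement*

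**What the plan says.** Amendment 2, section E4, under major complications occurring within 72 hours, states: "Bleeding is defined as major based on 1 or more of the following". The list has four entries:

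- a transfusion of two or more units
- "Decrease in hemoglobin level by greater than or equal to 2.0 g/L"
- a reoperation or invasive intervention
- bleeding at a critical anatomic site

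The Table of Abbreviations expands g/L as "grams per liter". The same number and unit stand in version 1.0 and Amendment 1. Amendment 2 added wording to the infarction and unstable angina definitions in E4 but left this line alone.

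Major bleeding is a component of the primary endpoint (SAP 7.1), of secondary endpoint #1 (SAP 7.2.1, which takes in every primary component) and of secondary endpoint #4 (SAP 7.2.4). The complication "must occur during or within 72 hours following the test or procedure" to qualify. Protocol E5 has the blinded committee adjudicate "based on the definitions presented above". SAP 7.1 sets no hemoglobin threshold of its own: "Definitions for each of the events are outlined in the study protocol as well as in the CEC charter". The charter is not among the documents.

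**The concern.** One criterion is enough, so the weakest one sets the effective threshold. A fall of 0.2 g/dL is a tenth of what the same number would mean in g/dL, and it sits beside criteria that all describe serious bleeding. For any bleed with paired hemoglobin values, the other three criteria become nearly redundant.

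The affected cases are minor bleeds, typically at an access site, with a small measured fall. Under the text they are primary events with the same weight as a death or an infarction. Protocol C4 explains that peri-procedural complications are included because they capture harm from invasive work-up. Over-counted bleeds would therefore follow the number of procedures in each arm. If the arms have similar volumes, the extra events dilute the comparison; if not, they bias it. Blinding does not help, because a blinded committee applying this threshold still counts the event.

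**Working it through.** **1. The unit.** The threshold is a definition, so there is no derived figure to reproduce. The conversion is 2.0 g/L ÷ 10 = 0.2 g/dL. On an assumed baseline hemoglobin of 120 to 160 g/L (not in the documents), the relative fall is 2/120 = 1.7% to 2/160 = 1.25%. The same number in g/dL would be 20 g/L, or 16.7% to 12.5%.

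**2. Non-inferiority, illustration only.** Protocol F1 gives 5,000 per arm, a 9% functional-arm rate at 2.5 years and CTA 10% better. That is 5,000 × 0.09 = 450 functional events and 450 × 0.9 = 405 CTA events. The margin is 1.10, judged on the upper limit of the two-sided 95% confidence interval (SAP 7.1). A count-based approximation, ignoring loss to follow-up, is

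upper limit = (a/b) × exp(1.96 × √(1/a + 1/b)), with a CTA events and b functional events.

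The numbers of extra events and their splits are assumed. All extra events are treated as new first events, with no overlap with existing ones.

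| Extra events (CTA + functional) | a vs b | HR | Upper limit | Below 1.10? |
|---|---|---|---|---|
| 0 | 405 vs 450 | 0.90 | 1.03 | yes |
| 120 (72 + 48) | 477 vs 498 | 0.96 | 1.09 | barely |
| 210 (126 + 84) | 531 vs 534 | 0.99 | 1.12 | no |
| 210 (105 + 105) | 510 vs 555 | 0.92 | 1.04 | yes |
| 210 (84 + 126) | 489 vs 576 | 0.85 | 0.96 | yes; also below 1.00 |

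The split matters more than the total. An even split hardly moves the limit. A 60:40 split toward CTA loses non-inferiority, and the reverse split would produce a superiority finding.

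**3. Superiority, illustration only.** The design case is 9% vs 7.2% with 3% loss, so 4,850 per arm. Power by Schoenfeld is Φ(√(D/4) × |ln HR| − 1.96), with HR = ln(1 − q)/ln(1 − p) and D = 4,850 × (p + q), where p and q are the functional and CTA rates.

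- No extra events: D = 785.7, HR 0.792, power 90.4%. This matches the plan's aim of at least 90%.
- 1% extra in each arm: p = 0.09 + 0.01 × 0.91 = 0.0991, q = 0.072 + 0.01 × 0.928 = 0.0813, HR 0.812, power 86.7%.
- 2% extra in each arm: p = 0.1082, q = 0.0906, HR 0.829, power 83.0%.

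**The case against.** **The criterion grades a bleed; it does not create one.** This stands. A reader might infer that most catheterized patients with a repeat hemoglobin would become primary events. The documents do not support that. The lead-in in E4 presupposes bleeding. The assessment table in E2 schedules no hemoglobin at any visit. The day-60 and six-monthly contacts ask about major bleeding as part of the interval history, so a case has to be recognised and reported before the committee sees it. What remains is that E4 sets no test for overt bleeding, and a reported minor bleed with a small fall still qualifies.

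**The charter may carry a different threshold.** It may, and then actual adjudication could be sound. But the SAP names both protocol and charter as sources, so they would conflict, and E5 points to the protocol.

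**The size is unsupported.** This also stands. The documents give no catheterization rate, no share with paired hemoglobin, no distribution of falls and no split by arm. Even the direction is open, because protocol B1 section 1.c expects CTA to spare patients without disease further invasive testing. A reader might also infer that the slip would overturn non-inferiority when the arms are truly equal. It would not need to: with an assumed 350 events per arm the upper limit is already exp(1.96 × √(2/350)) = 1.16, so non-inferiority fails without any extra events.

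**Other analyses would expose the problem.** Secondary endpoint #2 leaves these complications out, and SAP 7.2.4 tabulates each complication separately. An inflated bleed count would therefore be visible, but seeing it afterwards does not repair the primary result.

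**Conclusion.** The criterion is wrong as written and should be settled before the final analysis. That conclusion rests on the text alone: the unit is spelled out, any one criterion suffices, no later version changes it, and the component enters the primary endpoint and secondary endpoints #1 and #4. The tenfold slip is a strong inference from the companion criteria. A reader might take 20 g/L as the proven intention, but no passage states the intended value, so none is asserted here.

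The effect on the trial is unknown. It could be negligible if few reported bleeds rest on hemoglobin alone, or if the charter already differs. The calculations show direction and sensitivity under assumed numbers of extra events, using event counts from the 2.5-year rates in F1: modest dilution if the arms are balanced, and a possible change of conclusion if they are not.

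**What to change.** Compare the hemoglobin unit and threshold in E4 with the CEC charter and make the two agree. If g/dL was intended, correct E4 and record the correction in the SAP's list of changes from the protocol (section 17). Before the final analysis, have the blinded committee list every bleed that qualified on the hemoglobin criterion alone and re-check it against the reconciled definition. State in the clinical report how many there were and how many changed.

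The cost is a unit correction and what should be a short case review. No new data collection is needed beyond the source documents already held for adjudicated events.

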***Invasive catheterization without obstructive coronary artery disease***

Only the results of the initial (first) invasive cardiac catheterization that occurs within the first 60 days following randomization will be considered for the secondary endpoints which include invasive angiography without obstructive disease. The absence of obstructive disease is defined as no stenosis  $\geq 50\%$  in any major epicardial vessel including side branches  $\geq 2$  mm in diameter.

***Radiation Exposure Safety Endpoint***

Cumulative radiation exposure will be collected as follows:

- CTA: the actual administered dose (computed tomography dose index volume and dose length product for CTA) will be recorded by sites and confirmed by extracting information directly from the images.
- Nuclear imaging: the injected/administered contrast agent dose will be recorded and standard tables used to convert into equivalent doses for appropriate comparison with CTA.
- Invasive coronary angiography and intervention: the actual administered radiation dose or fluoroscopy time will be recorded by sites and standard tables used to convert into equivalent doses for appropriate comparison with CT.

These measures will ensure accurate calculation of the actual cumulative radiation exposure in each arm for tests performed for the diagnostic work-up during the 60 days following enrolment. In addition, we will capture all cardiac diagnostic testing involving radiation performed during the entire follow-up period (CTA, nuclear cardiology, catheterization) and will estimate cumulative radiation exposure over the entire trial using our original data collection (average dose per test for each site) to extrapolate radiation exposure during follow-up.

***E5 Independent Clinical Event Adjudication Committee***

An independent clinical event adjudication committee will review and adjudicate all primary endpoint events and the catheterization secondary endpoints in a blinded fashion based on the definitions presented above. If the invasive cardiac catheterization report is inconclusive, the CEC will review the catheterization films for a visual assessment of CAD. The other clinical secondary endpoint events and cumulative radiation exposure will not be adjudicated.

Primary outcome events will be documented through 60 (+/- 14) days after randomization by the site Investigator or authorized designees. After that, the DOFG or its designees will be responsible for documenting study events from 6 months until the end of the study.

---

## E6 *Quality-of-life Assessments*

Baseline QOL interviews will be administered to ~6000 subjects enrolled (prior to July 2012) by site personnel as soon as possible after consent, preferably before the subject's randomization. Completed questionnaires will be sent directly to the EQOL CC for data processing. Follow-up QOL questionnaires will be administered via structured telephone interview by DOFG trained and supervised interviewers at 6 months, 12 months, and 24 months post-randomization (among patients followed for 24 months). Proxy QOL questionnaires will be used when a subject has died in the follow-up interval or has become incapacitated; these questionnaires will include items that can be reliably obtained from a relative, caretaker, or medical record. Proxy questionnaires will be used if the subject is unable to participate in follow-ups via telephone interview.

### *Content of Health-related Quality-of-life Questionnaires*

A battery of validated instruments will be used that build on a disease-specific core supplemented with generic measures to provide a comprehensive but brief assessment of health-related QOL.

Chest-pain-specific symptoms will be measured using the **Seattle Angina Questionnaire (SAQ)**, a 19-item instrument that assesses 5 dimensions of the impact of chest pain on QOL: physical limitations, angina stability, angina frequency, treatment satisfaction, and disease perception. The **Duke Activity Status Index (DASI)**, a 12-item scale that has been validated in cardiac patients against maximal oxygen uptake measured at exercise ( $\text{VO}_2$  max), will be used as a disease-specific functional status assessment. The 4-item **Rose Dyspnea Scale** will be used to assess patients' levels of dyspnea with common activities.

The generic core instrument to be used is the **Medical Outcomes Study Short Form (SF-12)**. The SF-12 is composed of 8 scales (physical function, role function–physical, role function–emotional, general health, bodily pain, social function, psychological well-being/mental health, and vitality), a health transitions item, and 2 summary scores. Additionally, the entire scales for general health, psychological well-being, vitality, and social functioning from the SF-36 health survey will be used to provide better resolution of any treatment differences in these domains.

To assess effects of the 2 diagnostic strategies on the prevalence of depression, we will employ the **Patient Health Questionnaire (PHQ)**, a 9-item depression scale that has demonstrated good agreement with the clinical diagnosis of depression.

Patient-specific utilities will be assessed using the **EuroQoL-5D (EQ-5D)**, a standardized generic health-status measure that links specific health states to general population-based utilities. The EQ-5D consists of a 5-dimension health-state assessment, which allows for definition of 243 discrete health states that can be mapped to population utility weights and a self-rating (0-100) "thermometer" of current health-related QOL. The EQ-5D will be collected as part of all QOL questionnaires.

Employment/productivity will include time lost from work and reduced productivity while at work as measured by the 6-item **Stanford Presenteeism Scale** and questions adapted from the NHLBI Bypass Angioplasty Revascularization Investigation Substudy in Economics and Quality of Life.

---

